| 1. **Sample size considerations**   The main effects of interest in this study are the protective effect of antibiotic treatment (ORAB) and how this effect differs by co-morbidity (ORCO; i.e. the interaction between antibiotic treatment and co-morbidity).  Below, we derive sample sizes needed to detect these effects at 5% significance and 80% power (see Appendix Sample Size Calculation for detailed information on calculations and assumptions). We do so first for COPD patients with a respiratory infection based on previously published effect sizes. We will then relate these sample sizes to patients with other co-morbidities and with urinary or skin/soft tissue infections.  **Respiratory infections**  The power to detect any protective effects depends heavily on the risk of developing the outcome in question.  Past studies looked at a range of individual outcomes, including some extremely rare outcomes with risks as low as 0.04% (e.g. mastoiditis after URTI). They found average effect of antibiotics of ORAB = 0.69.11 and a sample size of ***971,057*** is required to detect this effect in our study.12 To be able to further investigate interactions, i.e. is the protective effect of antibiotics against rare outcomes such as mastoiditis different in patients with COPD versus no COPD, a sample size of **approx. 14 million** patients would be required.13 This is beyond the scope of this study.  Within this study, we will not consider effect sizes in rare outcomes such as mastoiditis individually. Instead, we will look at composite outcomes relevant to patients who consulted for infections, i.e. outcomes such as re-consultations, hospitalisations, etc. (see M. Exposures, Health Outcomes§ and Covariates for details). The risk for these outcomes is much more likely to be around 2.4% previously found for pneumonia.11 For this risk, required sample sizes for the protective effect of antibiotic treatment (ORAB) and how this effect differs by co-morbidity (ORCO) reduce to ***16,512***and ***258,247***.  Assuming a total sample size of at least 3,355,353 found previously (based on only 162 practices11), this study will be powered to detect ORAB and ORCO as small as 0.975 and 0.83, i.e. we will have the power to detect a protective effect of antibiotics against adverse outcomes as small as 2.5% and an increase in effects of antibiotics by 17% points in co-morbid patients.  **Urinary tract and skin/ soft tissue infections**  There are roughly 1/5 as many cases of urinary tract infection and 2/5 as many cases of skin/soft tissue infections as compared to respiratory infections.14 This translates into 671,070 cases of urinary and 1,342,141 cases of skin/ soft tissue infection. No published figures on effect sizes in urinary or skin infections could be found. Assuming similar effect sizes as in respiratory infections, the numbers for both kinds of infection well exceed the minimum sample size of 258,247 needed.  **Other comorbidities**  The powers to detect the same effects for diabetes, CKD, asthma, smoking and obesity are expected to be the same or higher, given the higher prevalence for these conditions (H. Feasibility counts). |

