| 1. **Plan for addressing confounding**   In objectives 1-3 the aim is to describe rates and undertake descriptive analyses rather than to make inferences about the effect of antibiotic treatment, which is the purpose of objectives 4 and 5. For this reason the issue of confounding is only relevant to objectives 4 and 5.  Individuals who are at higher risk of complications will be more likely to be prescribed antibiotics by their GP (i.e. confounding by indication), introducing a systematic difference between those who are treated and not treated with antibiotics. In this scenario, untreated cases will be less likely to experience adverse events irrespective of their exposure to antibiotics, tending to underestimate the protective effect of antibiotics. We will use propensity score methods to attempt to adjust for this issue. These methods are increasingly used to mitigate the consequences of non-random allocation of treatment in observational studies by modelling the a priori probability of each patient to receive the treatment.  We will use the treatment propensity scores to perform an inverse probability of treatment weighting to account for baseline differences in treated and untreated participants. This will enable assessment of absolute risk and numbers needed to treat to prevent re-consultation and hospitalisation in different groups.19 Propensity score weighting in effect produces a synthetic sample in which the distribution of measured baseline covariates is independent of treatment assignment. Presentation and analyses of results are very similar to a randomized trial allowing assessment of absolute risk and numbers needed to treat in different groups.  In order to create appropriate propensity scores, we will attempt to capture indicators for severity of disease and patients’ risk of complication, such as prior hospitalisation and immunosuppression. Measures such as vital signs are usually poorly recorded which can hamper efforts to estimate disease severity. To overcome this issue we will use GP prescribing preference as an instrumental variables, as described by Davies et al 2013.20  Besides confounding by indication, a number of further factors might influence prescribing. The decision to prescribe an antibiotic is a complex process, depending on multiple characteristics on the patient and practice level. Patients’ demographic factors, patients’ attitude towards antibiotic prescribing, physicians’ workload, date of consultation and geographic location of the practice have been found to influence physicians’ prescribing decisions.21 The use of further instrumental variables may help to estimate the impact of these factors in our analysis and we will also control for differences in prescribing habits between practices through the application of random effects models taking account of potential correlation within multiple episodes of the same patient and between patients within the same practice.  Acknowledging that differences in practice prescribing do not necessarily constitute actually differing prescribing habits but might instead reflect underlying differences in coding, we will undertake an exploratory analysis to look at variation between practices graphically. Using a novel approach we will visualise variability between multiple data-generating sources (i.e. practices) that was specifically designed and tested for multitype, multivariate and multimodal biomedical data.22,23 Where outlying practices are identified, analysis will be re-run without those practices and results presented with the analysis outlined in *N. Data/ Statistical Analysis*. |

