| 1. **Limitations of the study design, data sources, and analytic methods**   The aim of this study is to make inferences about the effect of antibiotic treatment overall, and in different patient groups in order to develop models to support antibiotic prescribing decisions in primary care. The major challenge is to adjust for confounding by disease severity, i.e. the fact that patients with more severe infections are more likely to be prescribed an antibiotic. Estimating disease severity in primary care is challenging because clinical measures such as vital signs are not well recorded. We have outlined methods to try and account for this issue including the use of instrumental variables and treatment propensity scores.  This study will be limited to some extent in the outcomes it will be able to investigate. First, as shown in I. Sample size considerations, the power needed to identify differences in treatment effects by co-comorbidities will be limited by sample sizes available for extremely rare outcomes. However, as we have chosen our outcomes based on their importance for patients requesting antibiotics, we will look at more common outcomes like re-consultation for which sample sizes should be sufficient. The final effect sizes that we will be powered to detect will then depend on the actual number of observations for respiratory, urinary and skin/soft tissue infections. We will take this a priori power into account when discussing our findings. Secondly, we will rely on the representativeness of the data sources from which we obtain our outcome measures. In particular, HES A&E data coverage is incomplete in comparison to national A&E attendances. We expect this to bias our results for A&E consultations towards the null, limiting our power to detect true differences in outcomes. Again, this limitation will be taken into consideration when discussing any findings on A&E admissions.  By relying on clinical codes to define exposure and measure outcomes, this study may be subject to misclassification. It is known that considerable inter-practice variation exists in coding certain conditions. GPs may not use diagnostic codes to define every episode of e.g. URTI. We will aim to mitigate misclassification of URTIs and other infections by building on comprehensive code lists from previously published studies using CPRD and THIN and reviewing them with experts in the field (see Appendix Table 2). Even so, code lists may not always accurately represent the real reasons why antibiotics were prescribed, as much of the clinical information that is obtained during the consultation is not captured in them. However, one of the main aims of this study is to get a better understanding of this problem through linkage of prescribing and indication. This is further aided by exploring differences in coding between practices will be explored with novel methods, as described in *O. Plan for addressing confounding*.  Although the prescription data recorded in CPRD is of high quality, prescription records themselves do not guarantee that individuals will necessarily take the antibiotics. CPRD data describes antibiotics prescribed and it’s known that patients do not fill 100% of their prescriptions. With no valid way to estimate the proportion of prescribed CPRD antibiotics that were dispensed, we will be unable to ascertain which patients were adherent to the prescribed medications. Furthermore, the antibiotic prescription data used in this work is based on those prescribed from primary care, and thus does not take into account antibiotics prescribed from alternative healthcare sources, such as online, walk-in centres, and urgent care. |

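### The detectable odds ratios of 0.975 and 0.83 are best-case limits with no allowance for the weighted, adjusted or instrumental analyses planned for Objective 4

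*Protocol*

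**What the plan says.** Section I (Sample size considerations) names two effects of interest: the antibiotic odds ratio (ORAB) and its interaction with co-morbidity (ORCO). For these, "we derive sample sizes needed to detect these effects at 5% significance and 80% power". The planning effect comes from earlier work: "They found average effect of antibiotics of ORAB = 0.69.11" (the final digits are a reference number). Two risks are used. One is for "some extremely rare outcomes with risks as low as 0.04" per cent. The other is for the composite outcomes: "The risk for these outcomes is much more likely to be around 2.4% previously found for pneumonia.11". At 2.4% the required sizes are 16,512 for ORAB and 258,247 for ORCO. With at least 3,355,353 respiratory episodes, "this study will be powered to detect ORAB and ORCO as small as 0.975 and 0.83". The urinary (671,070) and skin (1,342,141) cohorts are described as comfortably above 258,247. The details are referred to an appendix that is not part of the document at hand.

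Section N, step 4, plans logistic mixed models. They adjust for covariates and for the probability of treatment, and account for clustering by practice and by patient. Section O adds: "We will use the treatment propensity scores to perform an inverse probability of treatment weighting to account for baseline differences in treated and untreated participants". Because severity is poorly recorded, it also says: "To overcome this issue we will use GP prescribing preference as an instrumental variables". The limitations section ties the detectable effects to the number of observations, then says: "We will take this a priori power into account when discussing our findings".

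**The concern.** The power statement appears to describe a crude comparison of treated and untreated episodes. Section O says that this comparison is confounded by indication. The analyses meant to answer Objective 4 generally have larger variance for the same number of episodes. Weighting makes some observations count far more than others, and an instrument uses only the part of the variation in treatment that it explains. If no allowance was made, 0.975 and 0.83 are limits for an analysis that the protocol does not intend to rely on.

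This matters because the protocol will use its a priori power when discussing results, and its purpose is to ask whether prescribing could safely be reduced in co-morbid patients. A non-significant interaction weighed against an optimistic power figure would look more reassuring than it is.

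**Working it through.** **Inputs from section I.** Significance 5% (taken as two-sided), power 80%, ORAB 0.69, risks 0.04% and 2.4% (taken as the risk in the untreated), N = 3,355,353, 671,070 and 1,342,141. The share treated, x, is not in the document and was back-solved.

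**Step 1: reproduce the plan's ORAB figures.** The unadjusted Wald formula for independent observations is

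N = (1.960 + 0.842)² × [1/(x·p1·(1−p1)) + 1/((1−x)·p0·(1−p0))] / (ln OR)²

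with (1.960 + 0.842)² = 7.849 and (ln 0.69)² = 0.1377.

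- p0 = 0.024, x = 0.80: p1 = 0.01668. The bracket is 76.19 + 213.46 = 289.65, so N = 7.849 × 289.65 / 0.1377 = 16,511.4. Printed: 16,512.
- p0 = 0.0004, x = 0.80: N = 971,056.9. Printed: 971,057.
- Solving for OR at N = 3,355,353 and p0 = 0.024 gives 0.9753. Printed: 0.975.
- With x = 0.50 the two sizes would be 11,817 and 698,278, which do not match.

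One value of x reproduces all three printed figures with an inflation factor of 1. No allowance was therefore applied to ORAB.

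**Step 2: ORCO.** The figures 258,247 and 0.83 depend on COPD prevalence, the COPD main effect and a planning ORCO, none of which is shown. Many input sets fit, so these figures are taken as printed.

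**Step 3: power at the quoted limits under variance inflation D.** A limit set at 80% power has

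power = Φ(2.802/√D − 1.960)

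and the detectable ORCO scales as 0.83^√D. The detectable ORAB is re-solved at N/D. For an instrument with first-stage partial R-squared R², D is approximately 1/R². The protocol gives neither weight variability nor instrument strength, so every D below is an assumption.

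| Assumed D | Power at the limits | Detectable ORAB | Detectable ORCO |
|---|---|---|---|
| 1 (as printed) | 80% | 0.975 | 0.83 |
| 1.25 | 71% | 0.972 | 0.81 |
| 1.5 | 63% | 0.970 | 0.80 |
| 2 | 51% | 0.965 | 0.77 |
| 3 | 37% | 0.957 | 0.72 |
| 10 (R² = 0.10) | 14% | 0.92 | 0.55 |
| 20 (R² = 0.05) | 9% | 0.89 | 0.43 |

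**Step 4: headroom over the required sizes.**

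- ORAB 0.69 (16,512 needed): 3,355,353/16,512 = 203-fold respiratory, 81-fold skin, 41-fold urinary.
- Interaction (258,247 needed): 3,355,353/258,247 = 13.0 respiratory, 1,342,141/258,247 = 5.2 skin, 671,070/258,247 = 2.6 urinary.

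To keep 80% power for the planned interaction, an instrument would need R² of at least 1/13.0 = 0.08 (respiratory), 1/5.2 = 0.19 (skin) and 1/2.6 = 0.38 (urinary). With headroom H, power is Φ(2.802·√(H/D) − 1.960). At D = 3 this is 74% in the urinary cohort. At D = 10 it is 89%, 52% and 30% in the respiratory, skin and urinary cohorts.

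**The case against.** The strongest reply is that nothing has been miscalculated. The printed ORAB figures are right for the formula used, and the unseen appendix may call them unadjusted. That stands as far as it goes, but section I presents the limits as what the study can detect, without that qualification.

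Other points also stand:

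- The respiratory N is given as a minimum from only 162 practices. A larger cohort could offset modest inflation, though offsetting an instrument with R² of 0.10 would take about ten times as many episodes.
- Clustering need not cost power. Treatment varies within practices and patients, so its effect can go either way.
- At 2.4% risk, an OR of 0.975 gives a treated risk of 2.341%, or an NNT of about 1,700. Losing power exactly there has limited clinical weight.
- Section N's significance tests come from the adjusted mixed model, section O ties weighting to absolute risks and NNTs, and nothing makes the instrumental estimate the test of the interaction.

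A reader might infer that the study as a whole lacks its claimed 80% power. The documents do not support that, given the headroom for the planning effects. A reader might also put a firm figure on the instrumental loss from the two-fold variation in practice prescribing mentioned in the background. That variation concerns practice prescribing rates, not the chance of treatment at an infection consultation, and the planned instrument is GP preference. Finally, nothing says that a null interaction will be read as proof of safety; that is a risk, not a stated plan.

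**Conclusion.** The point holds in a limited form. The 0.975 is an unadjusted, independent-observation limit with no margin. The 0.83 carries no stated allowance either, although its derivation cannot be checked. Neither should be presented as what the planned Objective 4 analyses can detect at 3,355,353 episodes. Under assumed inflation of 1.25 to 2, power at the limits is about 71% to 51%. With an instrument of assumed R-squared 0.10 it is about 14%.

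Detection of ORAB 0.69 is secure under any plausible weighting. The claim that the urinary and skin cohorts are amply large for the interaction is fragile mainly for urinary infection (2.6-fold headroom) and for any instrumental analysis. The sizes rest on the back-solved 80% treated, the printed 258,247 and 0.83, and assumed values of D and R-squared.

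**What to change.** In section I:

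- Label 0.975 and 0.83 as unadjusted best-case limits.
- State which estimate (adjusted, weighted or instrumental) carries the power claim.
- Restate detectable ORAB and ORCO for each syndrome over a stated range of variance inflation and first-stage R-squared.

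An approximate effective sample size from the fitted weights, and the first-stage R-squared, need only treatment, covariate and instrument data, so both can be obtained without looking at outcomes. The exact weighting inflation also depends on how the covariates relate to the outcome, so a range is still needed.

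In the limitations section, refer to the restated figures and to confidence intervals, and say that a non-significant interaction will not be taken as absence of a difference on the strength of the crude power.

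The cost is protocol wording and one short calculation, with no extra patients or data. The only downside is that the stated detectable effects become less favourable.

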| 1. **Exposures, Health Outcomes§ and Covariates**   **§***Please note:**Summary information on health outcomes (as included on the ISAC application form above) will be published on CPRD’s website as part of its transparency policy*  *Exposure*  Exposures will include i) prescription of an antibiotic ii) GP consultation for suspected infection (see Appendices: Table 1 – Codelist for antibiotics, Table 2 – Codelist categorising indications for antibiotic use and Table 3 – Codelists to identify patients with suspected respiratory tract, urinary tract or skin/soft tissue infection)  *Health Outcomes*  The following outcomes (within 28 days of presentation in primary care) will be separately considered for analysis:   - Re-consultation for the same type of infection (CPRD; see Appendix Table 3) - Re-consultation for a side effect of antibiotic treatment (CPRD; see Appendix Table 4a –side effects of antibiotic treatment) - Complications of infection in primary or secondary care (CPRD and inpatient HES; see Appendices: Table 4b and 4c – complications of infection; depending on the indication) - Admission to Accident & Emergency (HES A&E) - All-cause hospitalisation (inpatient HES) - All-cause mortality (CPRD, HES and ONS)   We will undertake a sensitivity analysis to investigate the impact of excluding outcomes that occur on the same day as the exposure. The impact of different time windows will be explored, informed by a literature review on the natural history of the duration of different infections.  *Covariates*  We will include the following covariates:   - Age (classified as 0-4, 5-17, 18-44, 45-64, 65-84, 85-94 and 95+, years of age inclusive) - Sex (female and male) - Index of Multiple Deprivation (IMD; 1-5) - Co-morbidities (coded as indicator variables based on national guidance from Public Health England3 and feasibility1; see Appendix Table 5 for comorbidity code list)   - Diabetes   - Chronic Kidney Disease (CKD)   - Chronic Obstructive Pulmonary Disease (COPD)   - Asthma - Obesity - Smoking status15 - Season (months or quarters) and year - Ethnicity   We will undertake a sensitivity analysis of the impact of coding co-morbidities as binary indicator variable and as total number of co-morbidities. |

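### Section I misstates the detectable antibiotic-by-comorbidity interaction: wrong scale for ORCO 0.83, a benchmark of 258,247 that fits an ORCO near 0.5, and a 2.4% risk that does not cover every outcome analysed

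*Protocol*

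**What the plan says.** Section I (Sample size considerations) names two effects of interest: the antibiotic odds ratio (ORAB) and its interaction with co-morbidity (ORCO). Sizes are derived "at 5% significance and 80% power", with COPD in respiratory infection as the worked case.

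- **Risk.** Section I sets single rare diagnoses aside: "Instead, we will look at composite outcomes relevant to patients who consulted for infections". It then adopts a risk: "The risk for these outcomes is much more likely to be around 2.4% previously found for pneumonia".
- **Required sizes at that risk.** 16,512 for ORAB and 258,247 for ORCO. No ORCO value is printed beside 258,247.
- **Detectable effects.** With at least 3,355,353 respiratory cases, "this study will be powered to detect ORAB and ORCO as small as 0.975 and 0.83". The second figure is glossed as "an increase in effects of antibiotics by 17% points in co-morbid patients".
- **Other syndromes.** Section I expects 671,070 urinary and 1,342,141 skin/soft tissue cases. Assuming effects similar to respiratory infection, it concludes that "the numbers for both kinds of infection well exceed the minimum sample size of 258,247 needed".

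Section M lists six outcomes, all-cause mortality among them, that "will be separately considered for analysis". Objective 4 in Section N fits a model to each adverse outcome. The Limitations section says: "We will take this a priori power into account when discussing our findings".

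**The concern.** A reader who looks in Section I for the interaction the study can detect finds one number, 0.83, and one benchmark, 258,247. The wording invites the reader to connect them, but they belong to sample sizes that differ 13-fold. The gloss on 0.83 puts it on a scale it is not on. The risk behind every figure is argued for composites, while the analysis takes outcomes one at a time.

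This matters because the statement will be used. Objective 4 calculates an NNT only where the antibiotic coefficient or its interactions reach p < 0.05, with values near 0.05 discussed separately. The Limitations section brings a priori power into the discussion of findings. The Amendments section bars NNT interpretation for the added comorbidities because their power is low. Applying that standard evenly requires knowing which of the original syndrome-comorbidity-outcome combinations are also weak. The study asks whether prescribing could safely be reduced in co-morbid patients, so a null interaction read as no difference would be a costly misreading.

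**Working it through.** **1. Reproduce the ORAB figures.** Inputs from Section I: 5% significance, 80% power, ORAB 0.69, risk 2.4% or 0.04%. Two-sided testing and an 80% treated share are inferred, because they recover the stated sizes. K = (1.960 + 0.842)² = 7.849.

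N = K × [1/(0.8·q(1−q)) + 1/(0.2·p(1−p))] / (ln OR)², where p is the untreated risk and q the treated risk.

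- p = 0.024, q = 0.01668: N = 7.849 × (76.19 + 213.46) / 0.1377 = 16,511 (stated 16,512).
- p = 0.0004: N = 971,057 (stated 971,057).
- Detectable ORAB at 3,355,353: 0.975 (stated 0.975).

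The method therefore matches the plan's.

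**2. Which ORCO belongs to 258,247?** By simple scaling, N is proportional to 1/(ln OR)². The ratio 3,355,353 / 258,247 is 12.99, with square root 3.60. So ORCO at 258,247 is 0.83^3.60 = 0.51.

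The full calculation uses the four treatment-by-COPD cells: N = K × Σ 1/(cell share × risk × (1 − risk)) / (ln ORCO)². The COPD share is not in the text. I solved for the share that makes 0.83 detectable at 3,355,353, which gives 2.1% if the COPD odds ratio is 1. ORCO at 258,247 is then 0.48. It stays between 0.46 and 0.50 for COPD odds ratios of 0.69 to 5 and for rounding of 0.83. Treated shares of 0.4 to 0.7 give 0.42 to 0.47.

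Two cross-checks:

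- At 0.04% risk the same inputs give 13.9 to 15.3 million (COPD odds ratio 4 down to 1), in line with the stated figure of about 14 million.
- A planned ORCO of 0.5 at 258,247 would give 0.825 (scaling) or 0.84 (full formula) at 3,355,353, close to the printed 0.83. A planned 0.69 would give about 0.90, and a planned 0.83 about 0.95. Neither fits.

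**3. What the urinary and skin cohorts can detect for COPD at 2.4% risk.** Scaling gives 0.83^√5.0 = 0.66 (urinary) and 0.83^√2.5 = 0.74 (skin). The four-cell formula gives 0.65 and 0.74. Power for 0.83 is Φ(2.80 × √(n/3,355,353) − 1.96): 12% at 258,247, 24% in urinary and 43% in skin. For the ORCO that has 80% power at 258,247, power is 99.5% in urinary and over 99.9% in skin.

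**4. Other comorbidities.** Assumption: each share is 2.1% multiplied by the Section H count over 36,119, the same in every cohort, with comorbidity odds ratio 1.

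| Comorbidity | Section H count | Share | Detectable ORCO, urinary / skin | Power for 0.83, urinary / skin |
|---|---|---|---|---|
| COPD | 36,119 | 2.1% | 0.65 / 0.74 | 24% / 43% |
| CKD | 79,056 | 4.6% | 0.75 / 0.82 | 45% / 74% |
| Diabetes | 107,382 | 6.2% | 0.78 / 0.84 | 56% / 85% |
| Asthma | 216,379 | 12.6% | 0.84 / 0.88 | 83% / 98% |
| Obesity | 358,930 | 20.8% | 0.87 / 0.90 | 95% / >99% |
| Smoking | 395,825 | 23.0% | 0.87 / 0.91 | 96% / >99% |

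Setting the comorbidity odds ratio to 2 or 3 moves these powers by about one percentage point at most.

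**5. The scale of 0.83.** The combined odds ratio in co-morbid patients is 0.69 × 0.83 = 0.573. The odds reduction goes from 31% to 43%, a change of about 12 points. The 17% is the relative fall in the odds ratio itself (1 − 0.83).

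**6. Dependence on risk.** Section I itself says that power depends heavily on outcome risk. As an illustration only, with risks that are not in the protocol, COPD power for 0.83 in the full respiratory sample falls from 80% at 2.4% risk to about 44% at 1%, 25% at 0.5% and 8% at 0.1%.

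**The case against.** The strongest reply is that Section I contains no false comparison. It ties 0.83 to the respiratory sample alone and never says that the urinary or skin cohorts can detect it. Those cohorts are 2.6 and 5.2 times 258,247, as claimed. A reader might infer that the power calculation is arithmetically wrong, or that these cohorts lack the power claimed for them. The documents do not support either: the two ORCO figures agree with each other if the planned value was about 0.5, and for that value both cohorts have over 99% power. The planned ORCO may also be stated in the sample size appendix, a separate file that is not shown. All of this stands, and it limits the point to what the sentence conveys.

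A second reply is that 24% and 43% describe COPD, the rarest of the listed conditions. This also stands. A reader might infer that comorbidity interactions in urinary and skin infection are underpowered throughout. The table shows otherwise: asthma, obesity and smoking pass 80% for 0.83 in both cohorts, diabetes does so in skin only, and CKD in neither.

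Third, the Limitations section says that detectable effects will depend on the numbers observed and admits weak interaction power for extremely rare outcomes. The respiratory size is given as a minimum. Nothing says that a null interaction will be read as no difference. This softens the risk of misreading but does not correct Section I.

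Finally, composite may have meant broad outcomes such as re-consultation or hospitalisation, as opposed to single diagnoses. That is a fair reading of the word. It still leaves one risk, taken from pneumonia, standing in for six outcomes that include death.

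**Conclusion.** Section I needs restating on three counts.

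- The gloss on 0.83 is wrong as written: the change in odds reduction is about 12 points at ORAB 0.69, not 17.
- The benchmark used for urinary and skin infection corresponds to an ORCO of about 0.48 to 0.51. Exceeding it says little about an interaction of the only size printed. For COPD, power for 0.83 is about 24% and 43%.
- The stated detectable effects hold at 2.4% risk and do not carry over to separately analysed outcomes with lower risk. Outcomes more common than 2.4% would do better.

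The first count is plain arithmetic. The second rests on the inferred 80% treated share, a COPD share back-solved from the protocol's own pair of figures, and the same share and 2.4% risk in all three cohorts. The by-comorbidity figures also assume the relative counts in Section H. None of the calculations allows for clustering, repeat episodes or weighting.

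**What to change.** In Section I:

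1. Print the ORCO behind 258,247. The value near 0.5 given here is inferred, so the planned value should come from the sponsor's own calculation.
2. Replace the urinary/skin sentence with a table of detectable ORCO by syndrome and comorbidity at 2.4% risk.
3. State that these figures do not hold for separately analysed outcomes with lower risk, and give the detectable ORCO at each Section M outcome's own assumed risk.
4. Replace the percentage-point gloss with a ratio of odds ratios of 0.83.

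In Section N (objective 4) or the Limitations section, commit to reporting interactions with confidence intervals, so that a null result in an underpowered syndrome-comorbidity-outcome combination is not read as no difference.

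The cost is some wording and one table, with stated power that looks less favourable. No extra patients are needed.
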